# Predicting unplanned hospital readmission in palliative outpatients (PRePP) – study protocol of a longitudinal, prospective study to identify informal caregiver-related and structural predictors

**DOI:** 10.1186/s12904-022-00955-y

**Published:** 2022-05-02

**Keywords:** Unplanned hospital admission, Palliative care, Specialized outpatient palliative care, Informal caregiver, Family caregiver, Psychological distress

## Abstract

**Background:**

Although the majority of German patients in a palliative state prefer to die at home, the actual place of death is most often a hospital. Unplanned hospital readmissions (UHA) not only contradict most patients’ preferences but also increase the probability of an aggressive end-of-life treatment. As limited knowledge is available which factors contribute to an UHA, the PRePP-project aims to explore predictors related to informal caregivers (IC) as well as medical and structural factors.

**Methods:**

This prospective, observational, mono-centric study will assess structural and medical factors as well as ICs’ psychological burden throughout seven study visits. Starting in April 2021 it will consecutively include 240 patients and their respective IC if available. Standardized measures concerning ICs’ Quality of Life (WHOQOL-BREF), psychological distress (NCCN-Distress Thermometer), anxiety (GAD-7) and depressiveness (PHQ-9) will be assessed. If participants prefer, assessment via phone, browser-based or paper-based will be conducted. Medical records will provide routinely assessed information concerning patient-related characteristics such as gender, age, duration of hospital stay and medical condition. Nurse-reported data will give information on whether hospitalization and death occurred unexpectedly. Data will be progressed pseudonymized. Multivariable regression models will help to identify predictors of the primary endpoint “unplanned hospital admissions”.

**Discussion:**

The PRePP-project is an important prerequisite for a clinical risk assessment of UHAs. Nevertheless, it faces several methodological challenges: as it is a single center study, representativity of results is limited while social desirability might be increased as the study is partly conducted by the treatment team. Furthermore, we anticipated an underrepresentation of highly burdened participants as they might refrain from participation.

**Trial registration:**

This study was retrospectively registered 19 October 2021 at clinicaltrials.gov (NCT05082389). https://clinicaltrials.gov/ct2/show/NCT05082389

## Background

With evolving treatment options in several diseases, prolonged survival at the cost of a more complex end-of-life treatment has been achieved in the recent past. In Germany, the need of adequate palliative care as well as the number of structures providing palliative care has increased [1]. In 2014, more than 33.000 cases were treated in specialized palliative care units, 30.000 in hospices and almost 87.500 cases were reported by specialized outpatient palliative care teams [2].

Between 52 and 94% of German patients prefer end-of-life care at their home [3, 4] while the actual place of death was home in less than one third of deceased persons [5] in 2009. Specialized outpatient palliative care teams (german abbreviation: Spezialisierte Ambulante Palliativversorgung, SAPV) aim to alleviate symptoms and enable incurably ill patients to stay at their familiar surrounding until death by providing sufficient end-of-life care. Evidence suggests various advantages of preventing patients dying in the hospital. Gomes et al. report that home palliative care increases the chance of dying at home and reduces symptom burden in particular for patients with cancer [6]. Quality of life tends to be higher in patients dying at home [7]. In addition, optimal care by informal caregivers (IC) leads to greater satisfaction and less grief on the part of the relatives [8]. Yet there is a limited understanding of comprehensive costs of palliative care [9], caring at home might relieve financial burden off the health care system as inpatient care accounts for more than 70% of costs [10] during a palliative phase.

Unplanned hospital admissions (UHAs) decrease the probability to die at home [11] and were identified as a factor of overly aggressive treatment near the end of life [12]. UHAs occur due to various reasons including physical, psychological and social factors as well as characteristics of professional support [6, 13]. According to Gamblin and colleagues [14], UHAs occur more frequently in patients being released from palliative care unit (compared to medical oncology ward), which is attributed to a more complex burden of symptoms. Evidence derived from lung cancer patients of a single center suggest UHAs are the result of cancer-related symptoms rather than treatment toxicities [15]. Gamblin et al. illustrated that living alone at home or the presence of at least one child at home were associated with death in hospital [14] while proposing that financial precariousness, exhausted or ill caregiver might contribute to readmission. Furthermore, UHAs caused by a medical indication can also be altered by the psychosocial factors at the patient’s place of residence [16]. A post-discharge palliative care consultation was associated with a significantly lower incidence of UHA [14].

The frequency of UHA as well as the place of death varies internationally [17]. These discrepancies can be explained both by different health care systems with a varying extent of hospice and palliative services [18] and by discrepancies of insurance coverage policies for hospital and palliative care [19–21]. The consensus of experts of the EAPC (European Association of Palliative Care) recommends a minimum of one SAPV-Team per 100.000 inhabitants, while in Germany only 0.22 SAPV-team per 100.000 inhabitants is available [22] with huge differences between federal states. In addition to specialized palliative care, there are further structures available in Germany: Alongside general practitioners and specialists, mobile nursing services and voluntary hospice organizations are involved in the care of palliative patients.

However, a major part of the care is provided by informal caregivers. This includes all family members, friends or neighbors who are involved in the care of a person with health-related restrictions usually without receiving payment [23]. In Germany, up to 4.7 million informal caregivers take care of a frail relatives [24], yet there is no structured evidence available how many of them support terminal-ill patients.

Yet recent research suggests that including informal caregivers in the disease management may improve patients’ outcomes [25], it might bear several burdens on the informal-caregiver [26]. These include physical symptoms such as decreased immune functioning, fatigue or sleep disturbance as well as high psychological distress, anxiety and depression [27, 28]. It remains unclear too which extent these burdens contribute to UHA as caregivers, often old or frail him-/herself, might be overwhelmed or too exhausted to provide sufficient care at home.

Overall, there is scarce evidence on factors associated with UHAs in palliative outpatients. It seems of utmost importance to prevent UHAs in order to meet patients' preferred place of death, alter support of the professional system according to the informal caregivers needs and provide economic responsible options for the treating hospital. This project will explore the role of medical, structural as well as caregiver-associated factors as predictors for UHA. It is an important prerequisite for both, clinical implications as well as further research activities.

## Methods/design

### Study design and setting

Starting in April 2021, the PRePP-project is a prospective, observational, longitudinal, single-arm, single center study to identify structural and medical factors as well as those related to a patient’s informal caregiver which predict (unplanned) hospital readmission.

Primary study aim is to explore structural, medical as well as IC-reported factors associated with UHAs. Secondary goals include the description of ICs’ psychological distress and supportive care needs.

This study is performed at the SAPV-team of a large tertiary cancer center treating about 300–330 palliative patients a year.

### Participants and recruitment

The PRePP-project aims to include two samples of participants, patients and their respective care providers. It aims to include consecutively 240 patients and, if present and consenting, their respective primary IC within 18 months.

Eligible patients who are adult (> 17 years), suffer from an advanced, life-limiting disease and are treated by the SAPV-team of our institution will be included.

The primary non-professional caregiver is defined as the adult person that provides most time supporting the patient regardless of being biological related or non-related. ICs can participate if they provide informed consent, are mentally and linguistically able to provide answers independently. IC-reported data can only be collected for patients with consenting ICs. Due to this condition the exact number of IC-participants cannot be predicted.

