### Statistical analysis

The primary endpoint "number of unplanned inpatient admissions" is account variable. Univariate Poisson regressions will be used to analyze the association of structural factors and relative-reported factors or structural data with the primary endpoint. With the planned patient number of 240, it is possible to detect changes of 50% (corresponding to rate ratios of 1.5 and greater, given a base rate of 0.85) with a power of 95% if the influence variable is a binary categorical variable with 50% probability of occurrence. For a binary factor with a probability of occurrence of 90%, the detectable rate ratio with 95% power is still 2.0. For continuous, normally distributed influence variables, rate ratios of > 1.25 are detectable with 95% power.

Since a large number of factors are to be tested, the adjustment for multiple testing seems reasonable. According to the explorative approach of the study, the control of the false discovery rate is done by Benjamini–Hochberg procedure. *P* values of the univariate regression analyses that are < 0.05 after adjustment with the Benjamini–Hochberg procedure are considered significant. In the multivariable model, all parameters whose *p* values from the univariate analyses are < 0.1 after adjustment should be analyzed. The *p*-values of the multivariable model will not be adjusted.

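### The single 95% power statement rests on 240 patients and is not limited to factors recorded for all of them, so it does not carry over to caregiver-reported factors

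*Protocol article*

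**What the plan says.** Under Statistical analysis, univariate Poisson regressions are planned to "analyze the association of structural factors and relative-reported factors or structural data with the primary endpoint", the endpoint being the number of unplanned admissions. The power statement comes next: "With the planned patient number of 240, it is possible to detect changes of 50" per cent, "corresponding to rate ratios of 1.5 and greater, given a base rate of 0.85) with a power of 95" per cent, "if the influence variable is a binary categorical variable with 50% probability of occurrence". It is extended to a second binary case ("For a binary factor with a probability of occurrence of 90%, the detectable rate ratio with 95% power is still 2.0") and to continuous, normally distributed factors with a rate ratio above 1.25, again with 95% power. No other sample size appears in that section.

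Under Participants and recruitment, 240 is the target for patients. Their primary caregiver joins only if there is one and that person consents. The article adds: "IC-reported data can only be collected for patients with consenting ICs". And: "Due to this condition the exact number of IC-participants cannot be predicted". Study visits and data assessment confirms that without a participating caregiver only record data, living situation and nurse-reported data are collected. Study design and setting places caregiver-reported factors in the primary aim, beside structural and medical ones.

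**The concern.** The power paragraph covers two kinds of factor but uses one denominator. Structural, medical and nurse-reported factors can be analysed in all 240 patients. The caregiver's quality of life, distress, anxiety and depression scores, and the caregiver characteristics, exist only for patients whose caregiver is present, able to answer and consents. The article does not expect this to be everyone. The Discussion part of the abstract says "we anticipated an underrepresentation of highly burdened participants as they might refrain from participation".

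What is at stake is how a null result is read. If caregiver distress shows no association with unplanned admission, a reader will set that against a claimed 95% power to detect a rate ratio of 1.25. For a predictor observed in a subset, that power was never computed.

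**Working it through.** **Inputs from the article (Statistical analysis).** N = 240; base rate b = 0.85; power 95%; rate ratio (RR) 1.5 for a binary factor with prevalence p = 0.5, 2.0 for p = 0.9, and 1.25 for a continuous factor.

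**Assumptions, because the article is silent.** Alpha of the power calculation 0.05, tried one-sided and two-sided. The continuous ratio is per standard deviation. Caregiver participation 50% to 90%, that is n = 120 to 216 pairs. No overdispersion and no adjustment for multiple testing.

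**Formulas.**
- Continuous factor, standard normal, β = ln RR: z = β·√(n·b·exp(β²/2)); power = Φ(z − z_α).
- Binary factor: V1 = 1/(b(1−p)) + 1/(b·RR·p); V0 = 1/(m·p(1−p)), with mean rate m = b(1−p+p·RR); power = Φ((√n·ln RR − z_α·√V0)/√V1).
- z_α = 1.645 one-sided, 1.960 two-sided.

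**Step 1: the article's own figure at 240.**
- Continuous, RR 1.25: β = 0.2231 and exp(β²/2) = 1.0252, so z = 0.2231 × √(240 × 0.85 × 1.0252) = 3.227. Power is Φ(1.582) = 94.3% one-sided and Φ(1.267) = 89.7% two-sided.
- Binary 50%, RR 1.5: V1 = 3.922, V0 = 3.765. Power 94.1% one-sided, 89.5% two-sided.
- Binary 90%, RR 2.0: V1 = 12.418, V0 = 6.880. Power 96.6% one-sided, 94.4% two-sided.

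With these formulas all three cases come within 2 points of 95% only at one-sided 0.05. Two-sided, only the 90%-prevalence case does. The baseline for judging the caregiver loss is therefore 94% (one-sided) or 90% (two-sided), not 95%.

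**Step 2: the same effects with n pairs.** In the continuous case z scales with √(n/240). For n = 120: 3.227 × √0.5 = 2.282, so power is Φ(0.637) = 74% one-sided and Φ(0.322) = 63% two-sided.

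| Participation (assumed) | n | Power, RR 1.25 per SD, one-sided | two-sided | RR per SD detectable with 95% power, one-sided | two-sided |
|---|---|---|---|---|---|
| 100% | 240 | 94% | 90% | 1.255 | 1.28 |
| 90% | 216 | 92% | 86% | 1.27 | 1.30 |
| 80% | 192 | 89% | 82% | 1.29 | 1.32 |
| 70% | 168 | 85% | 77% | 1.31 | 1.34 |
| 60% | 144 | 80% | 71% | 1.34 | 1.37 |
| 50% | 120 | 74% | 63% | 1.37 | 1.41 |

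Power for the binary factor with 50% prevalence and RR 1.5 is within about 2 points of these figures in every row (for example 85% and 77% at n = 168).

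**Step 3: loss due to caregiver participation alone.** Against the baseline of the same sidedness, 90% participation costs about 2 points one-sided and 3 two-sided. At 50% the cost is about 21 and 27 points. Power falls below 80% at under about 144 pairs one-sided (60%) or about 182 two-sided (76%).

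**The case against.** The strongest reply is that nothing is concealed. The article says outright that the caregiver number cannot be foreseen, it calls 240 a patient number and not a number of pairs, and the study is exploratory. On that view only a qualifying clause is missing. Much of this stands: the fault is a power statement that ignores a limit stated elsewhere in the same article, and the calculation for 240 is not itself wrong because of caregivers. But the qualifier matters, because the sentence just before the power figures names caregiver-reported factors.

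Four stronger readings are tempting, and the document does not support them.
- A reader might infer that power for caregiver factors is far below the claim. No participation rate is given, and at 90% participation the loss is only 2 to 3 points.
- A reader might infer that the whole question in the title is underpowered. Title and primary aim also cover structural predictors, the aim adds medical ones, and these keep all 240 patients.
- A reader might blame the entire drop from 95% on caregivers. Two-sided, power with 240 is already about 90% and the detectable ratio 1.28, so part of the gap comes from unstated sidedness.
- A reader might take the 1.25 claim to be mainly about caregiver scales. The sentence is generic, and the medical records also supply age, duration of previous hospitalization and number of team visits.

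The loss from the Benjamini–Hochberg adjustment is a separate matter. It affects all factors, and the article does not give the number of tests.

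**Conclusion.** The point holds in a limited form. The stated 95% power does not apply to caregiver-reported factors unless every patient has a participating caregiver. For those factors power is lower by an amount the plan cannot state, since the number of pairs is unknown. Over an assumed 50% to 90% participation, it is about 74% to 92% one-sided (baseline 94%) or 63% to 86% two-sided (baseline 90%) for a ratio of 1.25 per standard deviation. The ratio detectable with 95% power moves from 1.255 to between 1.27 and 1.37 one-sided, or from 1.28 to between 1.30 and 1.41 two-sided. The direction is certain for any participation below 100%; the size depends on the assumed participation and sidedness and on a Poisson endpoint without overdispersion.

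**What to change.** In Statistical analysis, limit the 95% statement to factors recorded for all 240 patients. For caregiver-reported factors, add a short table of power and detectable rate ratio over a range of pair numbers, for example 120 to 216. State the alpha and sidedness used, say that the continuous ratio is per standard deviation if that is what was meant, and show the baseline at 240 so that the effect of participation can be seen on its own. Once recruitment is complete, the actual number of pairs can be read off the table when null caregiver results are interpreted.

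The cost is a few sentences and one table. Design, recruitment and analysis stay as they are; the restated participation-related figures are less favourable for caregiver-reported factors only.

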### Study visits and data assessment

Data is obtained from three sources: (1) IC-reported, (2) medical-record based and (3) nurse-reported.

Data of consenting ICs will be obtained three times. Medical-record based and nurse reported data will be obtained seven times. Detailed timeline of study visits can be found in Fig. 1.

**Fig. 1 Fig1:**
[figure not shown]
Timeline of study visits and source of data. Data source red = medical record; blue = family care-giver; green = nursing practitioner

After informed consent, which will be obtained at the first regular visit of the SAPV-team (T0), the initial visit collects data of all three sources via tablet-PCs provided by SAPV-team at second home visit (T1). Two subsequent study visits after three (T4) and six months (T7) obtain IC-reported data remotely either browser-based, by mail (paper–pencil) or via phone by study staff. The monthly (T1-T7) assessment includes data derived from medical records and nurse-report.

If no ICs are available or refuse to participate, only the patient’s medical report, living situation and nurse-reported data will be gathered monthly (T1—T7).

Electronic data is captured applying REDcapp [29, 30].

### Ethics and trial registration

Ethical approval is obtained prior to recruitment from local institutional review board (BO-EK-320072020). According to German law (§34SächsKHG), no study specific informed consent must be obtained from patients to use routinely assessed data from medical records. This trial is registered at clinicaltrials.gov (NCT05082389).

### Study measures

Informal caregivers willing to participate answer standardized measures on several domains.

Quality of Life will be assessed administering the WHOQOL-BREF [31], a 26-items inventory to assess a person’s Quality of Life including the four domains physical health, psychological, social relationships and environment. Higher scores denote higher Quality of Life in this domain.

Psychological distress will be assessed by the NCCN-Distress Thermometer [32] which comprises of a visual analogue scale ranging from zero to ten with higher scores indicating a more severe burden and a checklist of various symptoms. It is extensively used and cut-off data is available for use in an oncological setting [32]. Preliminary, it was developed for use in cancer patients while it might be applicable in other settings as well [33].

Anxiety will be assessed applying the Generalized Anxiety Disorder 7-item scale [34], a seven-items patient-reported questionnaire with sufficient psychometric properties. Scores range from zero to 21 on a single scale with higher scores indicating a higher level of anxiety. Results can be classified in either one of four classes ranging from minimal to severe anxiety symptoms.

Depressivness will be measured administering the Patient Health Questionnaire [35], which comprises of nine items. A single sum score is calculated which ranges from 0 to 27 with higher scores indicating a higher level of burden. Results are categorized in four classes ranging from no depressive symptoms to severe symptomatology.

Due to the possible influence of the current COVID-19 pandemic, four self-developed questions considering IC’s worries regarding an infection, changes in professional support and psychological burden due to preventive measures such as wearing a face mask were administered.

Nurses will answer two surprise questions [36], predicting whether they would be surprised when the patient will die within the next month (first question) and whether an UHA will occur during the next month (second question).

Characteristics of IC such as age, gender, and kind of relation to the patient, duration of daily care, highest education, and employment status will be obtained. Furthermore, the amount and type of professional support such as mobile nursing teams will be assessed.

Medical records will provide routinely assessed information concerning characteristics of patient such as age, gender, diagnosis, duration of previous hospitalization, additional supportive services, number of visits by SAPV, symptoms status, admission (e.g. reasons, initiating person, admitting physician, planned vs. unplanned, which procedures applied).

### Statistical analysis

The primary endpoint "number of unplanned inpatient admissions" is account variable. Univariate Poisson regressions will be used to analyze the association of structural factors and relative-reported factors or structural data with the primary endpoint. With the planned patient number of 240, it is possible to detect changes of 50% (corresponding to rate ratios of 1.5 and greater, given a base rate of 0.85) with a power of 95% if the influence variable is a binary categorical variable with 50% probability of occurrence. For a binary factor with a probability of occurrence of 90%, the detectable rate ratio with 95% power is still 2.0. For continuous, normally distributed influence variables, rate ratios of > 1.25 are detectable with 95% power.

Since a large number of factors are to be tested, the adjustment for multiple testing seems reasonable. According to the explorative approach of the study, the control of the false discovery rate is done by Benjamini–Hochberg procedure. *P* values of the univariate regression analyses that are < 0.05 after adjustment with the Benjamini–Hochberg procedure are considered significant. In the multivariable model, all parameters whose *p* values from the univariate analyses are < 0.1 after adjustment should be analyzed. The *p*-values of the multivariable model will not be adjusted.

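### Poisson p-values, the Benjamini-Hochberg step and the power statement make no allowance for dispersion; if admission counts are overdispersed and ordinary standard errors are used, the false discovery rate exceeds 5%

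*Protocol article*

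**What the plan says.** All of the following is in the protocol article.

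- **Model.** Under Statistical analysis, the primary endpoint, the number of unplanned inpatient admissions, "is account variable. Univariate Poisson regressions will be used to analyze the association" with structural and caregiver-reported factors.
- **Use of the p-values.** The same section says that many factors will be tested and that the FDR is controlled by the Benjamini-Hochberg procedure. An adjusted p-value below 0.05 counts as significant. An adjusted p-value below 0.1 admits a factor to the multivariable model, whose own p-values are not adjusted.
- **Power.** With 240 patients, the design is said to detect effects "corresponding to rate ratios of 1.5 and greater, given a base rate of 0.85". The power claimed for this is 95%, for a yes/no factor present in half of the patients. No dispersion parameter appears.
- **Setting.** The Background states that "UHAs occur due to various reasons including physical, psychological and social factors as well as characteristics of professional support". Participants and recruitment describes adults with advanced, life-limiting disease. Study visits and data assessment describes monthly data collection from T1 to T7, about six months.

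The article does not name the type of standard error, a dispersion check or an offset for time at risk. It gives no variance or distribution of UHA counts.

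**The concern.** Ordinary Poisson standard errors are correct only when the variance equals the mean, given the predictors in the model. A model with a single predictor leaves all other causes of admission in the error. If those causes shift the rate, the variance exceeds the mean, the standard errors are too small and the p-values are too small. Benjamini-Hochberg takes its p-values as valid and cannot repair them.

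The plan uses these p-values twice, for declaring predictors and for choosing what enters an unadjusted multivariable model, so an error at the first step carries into the second. The Discussion presents the data as groundwork for a screening tool, so spurious predictors would have consequences after the study.

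**Working it through.** **Inputs from the article:** N = 240; base rate 0.85; rate ratio (RR) 1.5; a binary factor with 50% prevalence; stated power 95%; Benjamini-Hochberg at 0.05. **Assumed, because the article does not give them:** the dispersion φ = variance/mean, the number of factors (30), their independence, the number of real effects, and survival.

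**Step 1: the plan's own power figure.** With Poisson variance and 120 patients per level:

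- log(1.5) = 0.4055
- variance = 1/(0.85 × 120) + 1/(0.85 × 1.5 × 120) = 1/102 + 1/153 = 0.01634, so SE = 0.1278
- 0.4055/0.1278 = 3.172
- one-sided 5%: Φ(3.172 − 1.645) = 93.7%
- two-sided 5%: Φ(3.172 − 1.960) = 88.7%

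The stated 95% is reached to within 2 points only one-sided, before any multiplicity adjustment, and with variance equal to the mean. The power statement therefore leaves no room for dispersion.

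**Step 2: how much dispersion is plausible.**

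- *Omitted factors of the plan's own size.* A 50% factor with RR 1.5 has relative rates 1 and 1.5, mean 1.25 and variance 0.0625, so its squared coefficient of variation is 0.0625/1.5625 = 0.04. For k independent omitted factors, φ = 1 + 0.85 × (1.04^k − 1). This gives 1.03 (k = 1), 1.11 (3), 1.18 (5) and 1.41 (10).
- *Unmeasured differences between patients.* For gamma heterogeneity of variance θ, φ = 1 + 0.85θ. θ = 0.5 gives 1.43 and θ = 1.0 gives 1.85.
- *Death-truncated follow-up with no offset.* Simulation gives φ of about 1.5 for an assumed median survival of 2 months and about 1.8 for 1 month.

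**Step 3: effect on each test and on the FDR.** The per-test type I error with ordinary standard errors is 2 × (1 − Φ(1.96/√φ)). At φ = 1.5, for example, 1.96/1.225 = 1.600, which gives 0.11. The FDR comes from simulated studies with N = 240, mean 0.85, 30 independent 50% factors and Benjamini-Hochberg at 0.05.

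| φ | Type I error per test | FDR, all 30 null | FDR, 3 of 30 real (RR 1.5) |
|---|---|---|---|
| 1 | 5% | about 4.5% | 7% |
| 1.25 | 8% | 12% | 15% |
| 1.5 | 11% | 25% | 26% |
| 1.85 | 15% | about 40-45% | about 40-45% |
| 2 | 17% | 52-54% | 44% |

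The 7% in the first row is above the 4.5% (27/30 × 5%) expected from valid tests, because the real factors left out of each univariate model already add a little dispersion.

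The number of factors matters less than φ. With all factors null and φ = 1.5, the FDR is 20% with 10 factors and 29% with 50.

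**Step 4: the other direction.** At φ = 0.58 the type I error is about 1% and the FDR is near 0. The tests are then conservative and lose power.

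**Step 5: robust standard errors.** In the same simulations they bring the all-null FDR back to about 5-8%. The cost is power. Multiplying the variance in Step 1 by φ, two-sided unadjusted power for RR 1.5 falls from 89% at φ = 1 to 81% at 1.25, 74% at 1.5 and 61% at 2.

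**The case against.** The strongest reply is that the article names Poisson regression and nothing more. The standard error, a dispersion check and an offset are details that a journal article may leave to a fuller document. Robust standard errors are compatible with the text as it stands. This is correct, and a reader should not infer that the plan is known to use ordinary standard errors. What remains is that the article does fix the model behind the FDR claim, and its power figure does assume variance equal to the mean (Step 1).

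A reader might also infer that the heterogeneous causes named in the Background are bound to break the Poisson assumption, so that the FDR will not be controlled. The documents do not support that. They give no dispersion. Three to five omitted factors of RR 1.5 produce a φ of only 1.11 to 1.18, which means a type I error of about 6-7%. Under-dispersion would keep the FDR below its limit. The larger figures need further heterogeneity or unequal follow-up, and both are assumed.

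Unequal follow-up is in any case a separate matter. The article speaks of rates and rate ratios, which is compatible with an offset. With an offset in the model, that source of dispersion is dealt with.

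Finally, the study calls itself exploratory. That lowers the stakes, but the plan still claims FDR control and selects variables on these p-values. The caregiver scales are also probably correlated, so the independence assumed in the simulation is a simplification.

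**Conclusion.** The point holds conditionally. The univariate p-values, the Benjamini-Hochberg step and the power statement all rest on Poisson regression with no allowance for dispersion, in a setting where overdispersion is likely but not certain. If ordinary standard errors are used, a φ of 1.25 to 1.5 turns a nominal 5% test into about 8-11% and a nominal 5% FDR into about 12-25%. A φ of 1.85 gives about 15% and 40-45%. If φ is 1, the FDR is controlled; if φ is below 1, the cost is power. These sizes rest on assumed values of φ and on 30 independent factors. Because the remedy costs almost nothing and protects in both directions, it should be adopted without waiting to learn the dispersion.

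**What to change.** Keep the Poisson mean model. State that all univariate and multivariable models use robust (sandwich) standard errors, and that the resulting p-values go into the Benjamini-Hochberg step. Report a negative binomial model as a sensitivity analysis. If a fuller document already provides for this, a one-line statement is enough.

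Handle unequal time at risk separately, with a log-time offset if none is planned yet. Robust standard errors do not correct the estimates for different exposure times.

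The cost is one software option. No data collection changes, and robust standard errors leave the Poisson point estimates as they are. If counts are overdispersed, confidence intervals widen and power falls as in Step 5, so the power statement should be repeated over a range of φ. With 3 of 30 factors real, the share of real factors found after Benjamini-Hochberg with robust standard errors falls from about 46% at φ = 1 to 24% at 1.5 and 15% at 2.
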